## Predictable adverse events

Nutritional guidance on potassium restriction may cause hypokalemia.

## Emergency Reporting

Adverse events that occur within 84 days of the start of the protocol will be followed up until the adverse events improve.

Emergency Reporting

1) The principal investigator/co-investigator will take appropriate measures in the event of a serious adverse event. The co-investigator shall immediately report to the principal investigator, regardless of the causal relationship with the study drug.

2) The Principal Investigator shall immediately report the serious adverse event to the head of the medical institution and notify the Investigator of the Drug Provider. In addition, it will be reported to the Effectiveness and Safety Evaluation Committee as necessary.

3) The report format and procedures for adverse events and adverse events for which a causal relationship with the study drug cannot be ruled out shall be in accordance with the "Procedures for Serious Adverse Events (established by each institution)".

< Emergency Contacts>

Principal Investigator: [name]

Department of Pharmacy, Mie Chuo Medical Center

[name]

[contact] [contact] (Pharmacy Department)

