### Observation and Reporting Schedule

| item | Prescription Fulfillment  (Start of observation) |  |  | End of Observation Period |
| --- | --- | --- | --- | --- |
| Number of days elapsed since obtaining consent | Day1 |  |  | Day 84 onwards* |
| Obtaining Consent | 〇 |  |  |  |
| Questionnaire for awareness survey on the intake of potassium-containing foods | 〇  (Questionnaire 1) |  |  | 〇  (Questionnaire 2) |
| Nutritional Guidance on Potassium Restriction | 〇 |  |  | 〇 |
| Follow-up on Nutrition Guidance |  | 〇 | 〇 |  |
| Patient Background Verification | 〇 |  |  | 〇 |
| Checking blood test data | 〇 |  |  | 〇 |
| Confirmation of urinalysis data | 〇 |  |  | 〇 |
| Confirmation of oral medication | 〇 |  |  | 〇 |
| Measurement of resting blood pressure after the visit | 〇 | 〇 | 〇 | 〇 |
| Confirmation of adherence of potassium adsorbents | 〇 | 〇 | 〇 | 〇 |

*The date of data acquisition after 84 days after obtaining consent depends on the date of the patient's outpatient treatment, so it shall be after Day 84.

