### Exclusion Criteria

1. Patients who do not agree to participate in this study
2. Patients who have difficulty communicating
3. Patients with hypokalemia (serum potassium level less than 4.0 mmol/L)
4. Patients undergoing maintenance dialysis
5. Patients Bringing Refill Prescriptions
6. Patients taking potassium preparations internally
7. Patients who are not expected to continue to visit the insurance pharmacy in the study for more than 3 months

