# Burdens and anticipated risks and benefits to the study subjects

## Burden and anticipated risks to research subjects

This study is not applicable because it is not invasive.

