## Comprehensive evaluation of these and measures to minimize burdens and risks

Not applicable.

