# Whether or not there is compensation for health damage caused by the research

Although it is not considered that there is a possibility of health damage caused by the participation of the research subject, the principal investigator and the co-investigator will provide appropriate treatment and other necessary measures in the event of a health hazard to the research subject. In this case, the treatment will be covered by insurance, and the research subject will pay the medical expenses for the out-of-pocket expenses.

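### Hypokalaemia is the named predictable adverse event, yet risk is declared not applicable, and the 84-day follow-up rule meets the only scheduled post-baseline potassium at most on Day 84

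*Protocol*

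**What the plan says.** **On foreseeable harm.** Section 17.2 states: "Nutritional guidance on potassium restriction may cause hypokalemia". Section 8.1, under burden and anticipated risks, states: "This study is not applicable because it is not invasive". Section 8.3, on measures to minimise burden and risk, says only "Not applicable". Section 18, on compensation, says "it is not considered that there is a possibility of health damage caused by the participation of the research subject".

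**On adverse-event follow-up.** Sections 17 and 17.3 carry the same sentence: "Adverse events that occur within 84 days of the start of the protocol will be followed up until the adverse events improve". Section 3.6.3 (six-monthly report) and section 10.2 (incidence report by the principal investigator) also require adverse-event reporting, and neither sets a time limit.

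**On when potassium is seen.** The schedule in 3.6.2 marks blood data at Day 1 and at "Day 84 onwards". The two columns between are blank for that row. The footnote ties the last date to the patient's outpatient visit and sets no latest day. Section 3.6.1 says the laboratory values come from routine care and that no test is added for the study.

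**On the threshold.** The only definition of hypokalaemia is in the exclusion criteria (4.1.2): "Patients with hypokalemia (serum potassium level less than 4.0 mmol/L)".

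**On analysis.** Section 3.5.2 tests the mean before-after change in potassium. It also compares the backgrounds of patients whose potassium improved with those whose potassium did not, without defining improvement.

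**The concern.** The intervention is meant to lower potassium, patients may enter from 4.0 mmol/L upwards, and the protocol itself predicts that potassium may go too low. Two things then matter: that the document says consistently that this risk exists, and that the test able to reveal it lies inside the period for which adverse events must be followed.

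Neither is secured. The risk statements matter beyond wording. Section 6, item (6), requires patients to be told the anticipated risks. Section 17.1 decides whether a serious event is unpredictable from what the study plan and explanatory documents describe. An author working from section 8 and one working from section 17.2 would write different texts.

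The timing matters because a low potassium is found by a blood test. The one scheduled post-baseline test falls on or after the last day of the follow-up window, so the duty to follow an event until it improves does not clearly reach a low value first seen at the endpoint visit.

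**Working it through.** **1. The risk statements side by side.** 17.2: the guidance may cause a named harm. 8.1: anticipated risk does not apply. 8.3: measures against risk do not apply. 18: no possibility of health damage. Lack of invasiveness, the reason given in 8.1, does not remove a risk that comes from the dietary advice itself. The four statements cannot all stand.

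**2. The two windows.** Inputs: consent is Day 1 (3.1); recruitment runs from 1 December 2022 to 28 February 2023 (4.2); the study period ends on 31 May 2023 (3.3). I take the start of the protocol in 17.3 to mean each patient's Day 1.

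Day 84 = consent date + 83 days. Last possible study day = (31 May 2023 − consent date) + 1. Largest gap = last possible study day − 84.

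| Consent | Day 84 | 31 May 2023 is | Largest gap |
|---|---|---|---|
| 1 Dec 2022 | 22 Feb 2023 | Day 182 | 182 − 84 = 98 days |
| 28 Feb 2023 | 22 May 2023 | Day 93 | 93 − 84 = 9 days |

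The window covers Days 1 to 84 and the scheduled test covers Day 84 onwards, so they share at most Day 84. Counting 84 elapsed days instead moves each gap by one day (97 and 8) and changes nothing of substance. These gaps are upper bounds set by the calendar, not expected delays.

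**3. The planned effect.** Section 3.2.2 plans for a mean difference of 0.5 mmol/L with SD 1.0 and gives n = 34. With two-sided 5% and 80% power, the exact paired t calculation gives 34 (power 0.808; 0.795 at n = 33). The point does not depend on this figure; the 0.5 is carried into step 4.

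**4. How many values might lie below 4.0 at follow-up.** The protocol gives no baseline distribution, so this is assumption throughout. Baseline B is normal with mean m and SD 0.5 (the between-person figure cited in 3.2.2), truncated at B ≥ 4.0. Change C is normal with mean −0.5 or 0 and SD s. The quantity is P(B + C < 4.0 given B ≥ 4.0), by simulation.

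| m | s | Mean fall 0.5 | Of 40 | No mean change |
|---|---|---|---|---|
| 4.5 | 0.3 | 0.408 | 16.3 | 0.090 |
| 4.5 | 0.5 | 0.421 | 16.8 | 0.157 |
| 4.5 | 1.0 | 0.449 | 17.9 | 0.276 |
| 4.75 | 0.3 | 0.287 | 11.5 | 0.054 |
| 4.75 | 0.5 | 0.323 | 12.9 | 0.108 |
| 4.75 | 1.0 | 0.387 | 15.5 | 0.227 |
| 5.0 | 0.3 | 0.178 | 7.1 | 0.028 |
| 5.0 | 0.5 | 0.225 | 9.0 | 0.066 |
| 5.0 | 1.0 | 0.318 | 12.7 | 0.177 |

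The range is about 18–45% (7 to 18 of 40) under the planned fall and about 3–28% (1 to 11 of 40) with no mean change. The two ranges overlap, because everyone starts at or above 4.0 and ordinary variation alone takes some below it.

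**The case against.** The strongest reply is that no information is lost. The sentence in 17 and 17.3 says which events are followed until they improve. It does not say that collection or reporting stops at Day 84, and 3.6.3 and 10.2 require reporting without that limit. The follow-up potassium is the primary endpoint, so every low value is in the dataset. A result on Day 84 itself is inside the window, and routine tests or symptomatic events before then can still be reported. All of this stands. A reader might infer that the foreseen harm goes uncounted, or that adverse-event capture ends at Day 84; the text supports neither.

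A reader might also infer that every fall, however deep, counts as a success. Section 3.5.2 does not say so. It leaves improvement undefined and uses the split only to compare patient backgrounds.

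It is tempting, too, to take everyone entering between 4.0 and 4.5 as harmed. With an assumed mean of 4.5 to 4.7 and SD 0.5, that is 29–41%, or 11 to 16 of 40. But this treats a mean fall as the same fall in each patient, on a baseline the protocol does not give. Moreover, 4.0 mmol/L is an eligibility limit that the protocol labels hypokalaemia; nowhere is it an adverse-event criterion.

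Finally, a laboratory safety table may sit in a statistical analysis plan that is not at hand, so its absence from the protocol is no fault in itself. What the reply does not answer is the conflict among 17.2, 8.1, 8.3 and 18, and the mismatch between the 84-day rule and the blood-data schedule. Both lie in the protocol, and an analysis plan would not cure them.

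**Conclusion.** The point holds as two internal inconsistencies. First, hypokalaemia is called predictable in one section, while three others treat risk as absent or not applicable. Second, the follow-up rule and the only scheduled post-baseline potassium overlap at most on Day 84, so a low value first seen later (up to 98 days later for the earliest enrolment date, up to 9 for the latest) has no stated follow-up to improvement and no stated classification as an adverse event.

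The gaps in days rest on the protocol's own dates and on reading the start of the protocol as consent. The 18–45% and 3–28% rest wholly on assumed baselines and SDs of change. They show only that values below 4.0 at follow-up could be common enough to describe, and that in a single-arm study such a count cannot be read as harm caused by the guidance. The primary analysis is unaffected. The point is modest and cheap to correct.

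**What to change.** 1. Reconcile 8.1, 8.3 and 18 with 17.2, and check that the explanatory document for patients agrees with the result.
2. Align the adverse-event window in 17 and 17.3 with the end-of-observation blood test in 3.6.2, so that an endpoint value obtained after Day 84 is covered.
3. Have the sponsor state how a low endpoint potassium is classified and reported, and whether it can count as improved in 3.5.2. That is the sponsor's clinical decision, and no threshold or rule is proposed here.
4. Report beside the mean change the number and percentage below the protocol's own 4.0 mmol/L at baseline and follow-up, with an exact 95% CI. The baseline count should be zero under 4.1.2. Label the table as a description, not as a count of harm caused by the guidance.

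The cost is a few protocol sentences and one table from data already collected. The downside is a slightly less favourable safety statement.

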# Whether or not there is compensation for health damage caused by the research

Although it is not considered that there is a possibility of health damage caused by the participation of the research subject, the principal investigator and the co-investigator will provide appropriate treatment and other necessary measures in the event of a health hazard to the research subject. In this case, the treatment will be covered by insurance, and the research subject will pay the medical expenses for the out-of-pocket expenses.

# Measures to be taken regarding the provision of medical care after the conduct of the research

Treatment after the end of this study is not prescribed.

# Handling of research results related to research subjects

The results of this study will not be disclosed to the research subjects. This is because the study is exploratory and the significance of the results is not significant enough to inform the study subjects because there is currently a lack of certainty.

# Details of outsourcing research-related work and method of supervision of the contractor

Not applicable to this research because it is not outsourced.

# If there is a possibility that the samples and information obtained from the research subject will be used for future research that is not specified at the time of obtaining the consent from the research subject, etc., or that may be provided to other research institutions, that fact and the contents that are expected at the time of obtaining the consent

In order to check the accuracy of the data, the publisher of the paper may ask for the data, or it may be provided to researchers around the world to use the data (data sharing). In this case, the data will be processed so that individuals cannot be identified, and a correspondence table will not be provided.

# When monitoring and auditing are to be conducted, the implementation system and procedures

## monitoring

The study is not invasive, so no monitoring will be performed.

## audit

The study was not invasive, so no audits were conducted.

## Appendix

1. Dietary guidance: Explanatory documents on nutritional guidance for CKD

2. Questionnaire of the Awareness Survey on the Intake of Potassium-Containing Foods (Before the Intervention) (Questionnaire 1)

3. Questionnaire of the Awareness Survey on the Intake of Potassium-Containing Foods (Post-Intervention) (Questionnaire 2)
